#### Study setting

The trial will be implemented at Dutch healthcare institutions. The trial is primarily implemented at the Erasmus MC and is further being extended to Franciscus Gasthuis & Vlietland and Ikazia Hospital. Inclusion of other healthcare institutions in the greater Rotterdam area is ongoing.

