### Sample size

The CATCH trial, which employed similar incentive schemes as the standard arm of the current trial, reported 41.1% abstinence at 12-month follow-up in the intervention arm versus 26.4% among participants who only attended the training sessions.^13^ The PERSIST trial will be embedded in healthcare institutions, many of which are currently implementing smoke-free policies, which is expected to be an extra external motivator for cessation. As such the validated abstinence percentages are expected to be slightly higher than in the CATCH trial, that is, 45% and 30%, respectively. We expect that personalisation of the incentives will further increase effectiveness to approximately 50%. In order to detect this difference in validated sustained abstinence (ie, 50% vs 30%) with a power of 0.8 and an alpha of 0.05 and using 1:1 randomisation, a total of at least 186 participants are needed. Taking into account a 15% loss to follow-up due to unexpected employee turnover,^11 24^ 220 participants are required. Further taking into account the potential maximum deviation from a 1:1 allocation ratio which may arise due to the stratified block randomisation procedure used, the minimum sample size required will increase in proportion to the number of different hospitals included in the trial. As the trial aims to estimate the effect of personalised incentives compared with no incentives and not to estimate the effect of each individual scheme, skewed allocation among the schemes is not an issue and is therefore not accounted for in the required sample size.

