### Allocation

Within participating institutions, participants will be individually randomised 1:1 to either the control or intervention arm. Permuted block randomisation with varying block sizes of four and six is used. There are two stratification factors: participating institution and readiness-to-quit (preparation or contemplation stage). A computer-generated allocation sequence was provided by ALEA randomisation service, in collaboration with the Erasmus MC Clinical Trial Centre. The block sizes will not be disclosed so as to ensure allocation concealment. ALEA will not release the randomisation result until the patient has been recruited into the trial and all baseline questionnaires have been completed. Participants are informed about their allocation by email. Inherent to the intervention and study design, participants and outcome assessors will not be blinded to allocation. Group session trainers will be blinded to allocation and data will be anonymised before analysis.

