### Statistical methods

The primary analysis compares continuous smoking abstinence rates at 12 months after the group-based training session in the intervention arm against the control arm, following an intention-to-treat analysis. In secondary analyses, continuous smoking abstinence at 15 months is assessed to see if abstinence is sustained after the incentives stopped. All randomised participants will be included in the final analysis, those lost to follow-up will be classified as smoking except for an unavoidable loss to follow-up (eg, untraceable contact information or death, following the RS12).^23^ Generalised linear models with a logit link function will be used to assess the difference in the primary outcome between control and intervention arms at t=12 months and to account for clustering between hospitals.

Additionally, subgroup analyses will be performed to identify possible subgroup-specific effects of the intervention. Planned subgroup analyses are based on:

Readiness-to-quit. Preparation stage versus contemplation stage.^10 20^Degree of tobacco dependence. Fagerström score below 5 versus Fagerström score of 5 or higher.^19^Present bias. Delayed versus present reward preference. Delayed reward preference=more than 50% larger delayed reward is chosen or present reward preference=less than 50% larger delayed reward is chosen.^21 22^Income. Based on gross monthly income in €. Low income=below 1500 versus moderate/high income=above 1500.^30^Educational level. Based on the ISCED.^28^ Lower educated=ISCED 0–4 versus higher educated=ISCED 5–8.

Subgroup analysis is not included in the power analysis and therefore exploratory. For missing data on subgroup information, multiple imputations will be performed.

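### The stated primary model names only hospital, as clustering with no estimator given, and leaves out readiness-to-quit, the other stratification factor

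*Protocol article*

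**What the plan says.** All references are to the protocol article.

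- **Allocation.** Participants are randomised individually, 1:1, within institutions. "There are two stratification factors: participating institution and readiness-to-quit (preparation or contemplation stage"). "Permuted block randomisation with varying block sizes of four and six is used". The allocation is released only after the baseline questionnaires are complete.
- **Statistical methods.** The primary analysis is a generalised linear model with a logit link, used "to assess the difference in the primary outcome between control and intervention arms at t=12 months and to account for clustering between hospitals". Readiness-to-quit appears in this section only as the first of five exploratory subgroups.
- **Incentives.** Being in the preparation stage is listed among the values that go with higher quit percentages. No effect size is given.
- **Study setting.** "The trial is primarily implemented at the Erasmus MC and is further being extended to Franciscus Gasthuis & Vlietland and Ikazia Hospital". Further institutions in the region are still being sought, so the final number is open.
- **Sample size.** For 50% against 30%, "with a power of 0.8 and an alpha of 0.05 and using 1:1 randomisation, a total of at least 186 participants are needed"; after a 15% allowance for loss, "220 participants are required".

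**The concern.** Two things do not fit together.

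First, the design balances the arms on two factors, but the stated model takes up only one. The factor it omits is one that the protocol itself regards as prognostic. Stratified blocks make the arms more alike on readiness-to-quit than chance would. An analysis that ignores the factor does not use that gain: its standard error is slightly too large for the design, and some power is lost.

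Second, hospital is given the role of a cluster. Treatment is assigned to individuals and both arms are balanced within each hospital, so hospital is a stratum and not a unit of assignment. The wording does not say whether hospital enters as fixed effects, as a random intercept, or through GEE or cluster-robust errors. With as few as three hospitals these can give very different tests. If the choice is left open until outcomes are known, it could decide whether the primary result is significant.

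**Working it through.** **1. The plan's own figure.** Inputs from the Sample size section: 50% vs 30%, alpha 0.05, power 0.80, 1:1. Sidedness is not stated; two-sided reproduces the result. With the pooled-variance formula and a mean rate of 0.40:

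n per arm = [1.960 × √(2 × 0.40 × 0.60) + 0.842 × √(0.50 × 0.50 + 0.30 × 0.70)]² / 0.20² = (1.358 + 0.571)² / 0.04 = 93

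The total is 186, an exact match. Then 186 / 0.85 = 218.8, so 219, or 220 with equal arms. The plan is therefore an individual-level comparison with no design effect. Any reading of the primary model should deliver about 5% error and 80% power on that basis.

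**2. Assumptions that the document does not give.** 60% of participants in the preparation stage; readiness odds ratio (OR) from 1 to about 5; between-hospital SD of 0.3 on the logit scale; three to six hospitals with assumed sizes (for three: 140/45/35 or 74/73/73 at N = 220, and 118/38/30 at N = 186). Blocks of 4 and 6 were drawn within hospital-by-readiness strata, with 3,000 simulated trials per setting. Simulation error is about 0.4 points at 5% and 0.7 points at 80%.

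**3. Leaving out readiness-to-quit: type I error.** With overall abstinence of 30%, the total variance is 0.30 × 0.70 = 0.21. The within-readiness variance is 0.6 × p₁(1 − p₁) + 0.4 × p₀(1 − p₀), where p₁ and p₀ are the rates in the preparation and contemplation stages. The type I error of a test that ignores readiness is 2Φ(−1.96 × √(total / within)). For OR 2 the rates are 0.356 and 0.216, the variance ratio (within / total) is 0.978, and the error is 4.75%.

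| Readiness OR | 1 | 1.5 | 2 | 3 | 4 |
|---|---|---|---|---|---|
| Variance ratio | 1.000 | 0.992 | 0.978 | 0.948 | 0.923 |
| Type I error, readiness ignored | 5.0% | 4.9% | 4.75% | 4.4% | 4.1% |

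**4. Leaving out readiness-to-quit: power.** Three hospitals, 186 analysed, 50% vs 30%:

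| Readiness OR | Hospital indicators only | Plus readiness | Gain (points) |
|---|---|---|---|
| 1 | 81.9% | 82.0% | 0.1 |
| 2 | 80.2% | 81.0% | 0.8 |
| 3 | 82.4% | 84.6% | 2.2 |
| 4 | 82.3% | 84.9% | 2.6 |

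A second set of simulations used N = 220, hospitals split 60/25/15, a treatment log odds ratio of 0.85 and 1,500 to 2,000 trials per setting. It gave 86.1% vs 86.8%, 81.7% vs 83.7% and 78.4% vs 82.3% for readiness log-odds of 0.7, 1.1 and 1.6 (OR about 2, 3 and 5). The gains are 0.7, 2.0 and 3.9 points.

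**5. Readings of the clustering wording: type I error.** The sandwich rows are a logit model with arm only and errors clustered on hospital.

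| Estimator | 3 hospitals | 5 hospitals | 6 hospitals |
|---|---|---|---|
| Hospital indicators | 4.0% to 5.1% | 5.1% | 5.0% |
| Hospital indicators plus readiness | 4.8% to 5.3% | 5.4% | 5.2% |
| Sandwich, normal reference, uncorrected | 26% to 30% | 18% | 15% |
| Sandwich, normal reference, G/(G−1) correction | 19% to 24% | 15% | 12% |
| Corrected sandwich, t reference on G−1 df | 5% to 8% | 7% | 6% |

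G is the number of hospitals. With a t reference on 3 − 1 = 2 degrees of freedom the error rate is roughly repaired, but power at 186 analysed falls to about 40% to 45%. A random intercept for hospital was not simulated.

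**The case against.** The strongest reply is that this is one sentence in a condensed article. The covariate list and the choice of estimator are commonly left to the analysis plan, which may exist and may settle both. That stands as far as silence goes: the article does not say that the model contains hospital and nothing else. What remains is that the article does state an adjustment, names one of its two stratification factors, and gives that factor the role of a cluster.

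A reader might go further and infer that the primary analysis breaks the 5% error rate. The document does not support that. It names no GEE, sandwich or cluster-robust errors, and a logit model with hospital indicators fits the wording equally well and holds about 5%. A reader might also infer that the omission makes the result invalid or the interval wider. It does neither. The test errs on the conservative side, and in a logistic model adjustment brings power, not a narrower interval for the log odds ratio.

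Two further replies are fair. Recruitment of other institutions is open, so three hospitals is the low end; with six, the sandwich reading gives 12% to 15%, about half as bad but still far from 5%. And the readiness effect is small: in the first set of simulations, power without readiness stays at 80.2% to 82.4% with 186 analysed, which meets the target.

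**Conclusion.** The mismatch between the Allocation and Statistical methods sections is real and should be corrected, but it does not invalidate the primary analysis. Omitting readiness-to-quit leaves a valid, slightly conservative test and costs about 0 to 4 points of power. The upper end needs a readiness odds ratio near 5, and the document supports only the direction of that effect. The larger issue is that the wording leaves the estimator open. One permitted reading, sandwich errors over a handful of hospitals with a normal reference, would give about 19% to 30% false positives with three hospitals and 12% to 15% with six. Hospital indicators give about 5%. That breach is conditional on an implementation that the document does not state. The figures rest on the assumed readiness split, hospital sizes and between-hospital variation listed above.

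**What to change.** In Statistical methods, replace the phrase about clustering between hospitals with an explicit model: logistic regression of 12-month abstinence on arm, institution and readiness-to-quit, all as fixed main effects, with model-based standard errors. Add a rule for pooling very small institutions, set without sight of outcomes by arm. If an analysis plan exists, it should say the same.

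Adjusting for the baseline Fagerström score is optional. It is not a stratification factor, and the point does not depend on it.

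The cost is a change of wording. Institution and readiness-to-quit are both known before the allocation is released, so no data collection or sample size changes. The change should be made before outcome data are examined by arm.

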### Patient and public involvement

Participants were not involved in designing the trial. Once the results are published, participants will be informed about the publication by email. This email will be drafted suitable for a non-specialist audience. Public involvement will be sought through the Erasmus Initiative Smarter Choices for Better Health initiative.

## Ethics and dissemination

The study protocol has been assessed by the Erasmus University Medical Centre Medical Ethics Committee (MEC-2019-0140). The committee decided that according to the Dutch Human Research Law (WMO), the protocol required no formal ethical approval. All participants will provide informed consent for participating in the study.

The results will be published in a peer-reviewed scientific journal. On completion of the trial and after the publication of the results, data requests can be submitted to the corresponding author at Erasmus MC, Rotterdam, The Netherlands.

## Discussion

We present the protocol of the PERSIST trial. The aim of the trial is to evaluate the effectiveness of personalised incentives in addition to group-based smoking cessation training on sustained smoking abstinence among hospital employees compared with group-based training alone. Personalisation entails that participants are advised and can choose from four different incentive schemes: standard, ascending, descending and deposit-based.

### Strengths and limitations

The PERSIST trial is unique in its approach to personalising incentives to promote smoking cessation. Strong links between personal characteristics and effectiveness of incentives to promote smoking cessation have been demonstrated previously, however, to our knowledge, the effectiveness of personalised incentives has not been studied before.^14^ Another unique element of the PERSIST trial is that participants receive personalised advice for an incentive scheme, based on personal characteristics, yet are free to deviate from the advised scheme. Voluntary choice with a personalised default is a common tool in behavioural economics to nudge people towards the scheme that is plausibly in their best interest.^31^ This feature is scientifically innovative in the context of smoking cessation programmes and importantly lets the treated individuals choose the scheme they will be enrolled.

By focusing on supporting smoking cessation among hospital employees, the PERSIST trial is executed in a highly relevant setting, as in light of the National Prevention Agreement, all university hospitals have to be smoke free by 2020 and all general hospitals by 2025.^32^ Finally, the PERSIST trial progresses from previous studies by extending follow-up beyond the last time point when incentives are provided to investigate if participants remain abstinent when incentives are no longer provided.

A limitation of the PERSIST trial is that participants from the intervention and control arm attend the same cessation support training sessions due to practical reasons, as slow inclusion rates otherwise would have caused long waiting periods between signing up and starting the training. Participants in the control arm might perceive this negatively and potentially drop out, causing attrition bias. Another consequence could be spill-over effects^33^; sharing of vouchers between control and intervention arm, leading to a double underestimation of treatment effectiveness. To avoid this, participants are informed about their status as early as possible to make sure they have time to accept their status. A third arm consisting of non-personalised incentives could have provided additional potentially valuable information on the effectiveness of personalised incentives versus incentives provided according to a fixed scheme. However, this option would have required an unfeasibly large sample size.
